## Abstract

**Background:**

Depression is a widespread and serious disease often accompanied by a high degree of suffering and burden of disease. The lack of integration between different care providers impedes guideline-based treatment. This constitutes substantial challenges for the health care system and also causes considerable direct and indirect costs. To face these challenges, the aim of this project is the implementation and evaluation of a guideline-based stepped care model for depressed patients with six treatment options of varying intensity and setting, including low-intensity treatments using innovative technologies.

**Methods/design:**

The study is a randomized controlled intervention trial of a consecutive sample of depressive patients from primary care assessed with a prospective survey at four time-standardized measurement points within one year. A cluster randomization at the level of participating primary care units divides the general practitioners into two groups. In the intervention group patients (n = 660) are treated within the stepped care approach in a multiprofessional network consisting of general practitioners, psychotherapists, psychiatrists and inpatient care facilities, whereas patients in the control condition (n = 200) receive routine care. The main research question concerns the effectiveness of the stepped-care model from baseline to t3 (12 months). Primary outcome is the change in depressive symptoms measured by the PHQ-9; secondary outcomes include response, remission and relapse, functional quality of life (SF-12 and EQ-5D-3 L), other clinical and psychosocial variables, direct and indirect costs, and the incremental cost-effectiveness ratio. Furthermore feasibility and acceptance of the overall model as well as of the separate treatment components are assessed.

**Discussion:**

This stepped care model integrates all primary and secondary health care providers involved in the treatment of depression; it elaborates innovative and evidence-based treatment elements, follows a stratified approach and is implemented in routine care as opposed to standardized conditions. In case of positive results, its sustainable implementation as a collaborative care model may significantly improve the health care situation of depressive patients as well as the interaction and care delivery of different care providers on various levels.

**Trial registration:**

This study is registered with ClinicalTrials.gov, number NCT01731717 (date of registration: 24 June 2013).

## Background

Depression is one of the most widespread mental disorders [1] and involves a high degree of personal suffering, a high burden of disease and serious impairments [2]. Thus it constitutes a substantial challenge for the health care system and causes considerable direct and indirect costs [3]. Detailed estimations predict a further increase in depression-related disease burden in the next 20 years; depression will represent the second most important factor for impairment and premature mortality after cardiovascular diseases in highly economically developed countries [2].

Health care is confronted with several central areas of concern in the diagnosis and treatment of depression:Depression often remains undetected or is diagnosed late: Especially in the primary care setting, the current detection rate of 50% to 68% needs to be optimized [4–8].Patients with depression often do not receive evidence-based treatments or the treatment is initiated only after a long delay [8,9]. Adults in urban areas have to wait 12.5 weeks on average for a first diagnostic contact, while in rural areas the waiting time for psychological treatments comprises up to 17 weeks, according to a national survey conducted by the German federal psychotherapist association [10]. Depressive patients on waiting lists suffer from a high burden of disease for many months [11].The initiation of treatment for patients with depression is often carried out with a rather unsystematic selection related to the type, the intensity of treatment and the adequate allocation of resources. This may increase the risk of undersupply on the one hand and oversupply on the other hand [12]. In this respect, especially low-intensity treatment options (e.g. structured self-help approaches) systematically integrated into the health care system are missing.When treatments are initiated, an integrated care spanning different sections of the health care system is complicated due to the fragmentation of health services and the absence of an appropriate interface management (e.g. between primary and secondary care and between out- and inpatient care) [13].

In order to overcome these deficits it is necessary to develop, implement and evaluate guideline-oriented and evidence-based models of care that include 1) better detection rates of depression, 2) the prompt offer and access to evidence-based treatments, 3) a systematic treatment selection with the option of choosing between different levels of treatment intensity to initiate a tailored and efficient treatment and 4) multi-professional cooperation of the providers across different health care sectors in order to ensure an integrated pathway through the health care system.

Stepped care is a promising approach for improved depression care [12,14,15], a concept recommended in national and international guidelines [16–18]. Stepped care is based on treating patients with the most adequate treatment of lowest intensity while continuously monitoring their treatment progress. If clinically necessary, patients are stepped up to a more intensive intervention form. The treatment level is adjusted gradually whenever indicated until a satisfactory health status is achieved [12]. Katon and colleagues [19–21] first demonstrated in the 1990s the effectiveness of several comprehensive models to improve the treatment of patients with depression in primary care: They found that a stepped care model consisting of psychoeducation and a higher frequency of psychiatric consultations led to increased medication compliance and reduced depressive symptoms in comparison to routine care, suggesting its effectiveness and cost-effectiveness [15,21]. Van’t Veer-Tazelaar et al. showed how a stepped care model (watchful waiting, bibliotherapy, short term psychotherapy and medication) for elderly patients with subclinical depression reduced the risk for the occurrence of a clinical depression by approximately 50% [22].

Taking these promising results into account, we developed and implemented an extended stepped care model into routine care integrating the following aspects:Implementation of a guideline-oriented and evidence-based stepped care model within a multi-professional network across different health care sectors consisting of general practitioners, psychiatrists and psychotherapists in out- and inpatient care.Systematic screening and structured diagnostic procedures in primary care as the basis for an appropriate delivery of different interventions following a stepped care approach.Patients are treated within this network with the goal of delivering a prompt and appropriate evidence-based treatment with an improved information exchange between the involved providers.Patients receive the treatment step which they are most likely to benefit from (as opposed to every patient receiving the least intense step first and being stepped up only if this step is not effective enough).Introduction of evidence-based treatment options with different levels of intensity which are not yet available in German routine care. We include modern e-health interventions like Internet- and telephone-based psychotherapy as well as the more traditional approach of bibliotherapy in the stepped care model [17,23].

The aim of the randomized controlled trial is to evaluate this guideline-oriented and evidence-based stepped care model for depressive patients comprising six treatment options of varying intensity and setting, including innovative technologies. The evaluation refers to the effectiveness and the cost-effectiveness of this complex intervention under the conditions of routine care.

## Methods/design

### Setting

The study is embedded in the intersectoral research network *psychenet: Hamburg Network for Mental Health* (2011–2014), a research and development project funded by the German Federal Ministry for Education and Research (BMBF) [24]. It aims at the improvement of the city’s population’s mental health by implementing new integrated health care networks based on evidence for effective treatment methods and by evaluating selected innovations and complex interventions in the region of Hamburg. The overall project is organized in 11 sub-projects. While the first five sub-projects (1–5) facilitate mental health across different areas of disease by improving information and education, fostering occupational health or strengthening the participation of sufferers and their family members, five illness-specific health networks have been conceived (sub-projects 6–10). A general accompanying sub-project (11) ensures the quality of the interventions in all sub-projects and conducts evaluative and health-economic investigations [24]. This article describes the study protocol of the health network depression (sub-project 7).

### Objectives

Primary objective of this randomized controlled trial is to examine the effectiveness of a complex intervention (stepped care model, SCM) assessed through the reduction in depression severity within a network of general practitioners (GP), psychiatrists and psychotherapists in routine care.

Secondary objectives are to examine the effectiveness of SCM in terms of response, remission and health-related quality of life as well as to examine its cost-effectiveness. Further objectives are the evaluation of the process quality and of patients’ and practitioners’ satisfaction with SCM.

### Study design

The study is designed as a randomized controlled intervention trial of a consecutive sample of depressive patients from primary care assessed with a prospective multiple time point survey. GPs are divided into two groups by undertaking a cluster randomization on the level of the participating primary care units. Patients recruited by GPs in the intervention group (IG) are treated within the stepped care approach (SCM, see section *Intervention*). Patients recruited by GPs in the control group (CG) receive treatment as usual (TAU). Both patient groups are compared with respect to their treatment response within a one-year period. The scientific approach is primarily quantitative with additional qualitative analyses regarding feasibility and acceptance of the SCM by patients as well as by out- and inpatient care providers.

### Primary hypothesis

The trial evaluates the primary hypothesis that the SCM condition (IG) outperforms the TAU condition (CG) regarding the primary outcome parameter (PHQ-9), i.e. that stepped care is more effective than treatment as usual in depressive symptom reduction after 12 months.

### Randomization

Cluster-randomization is performed in order to allocate confounding variables in equal parts to both study conditions and thus to control for potential bias in order to guarantee internal validity. In this study, cluster-randomization is undertaken at the level of the participating GP practices, which are allocated to either IG or CG in a 3:1 ratio. The process of randomization is conducted by a computer program by minimization based on the GP’s practice size (single practice vs. group practice), the location of the practice within Hamburg classified into the two categories (central vs. peripheral) and income level of the practice’s local district classified into three categories (low, middle and high). Criteria for selection of clustering variables are relevance and availability. We assume that each GP in the 49 participating practices is able to recruit 15–25 patients. A total of 36 practices is randomized into the IG and 13 practices into the CG.

### Ethical approval

The study protocol was approved by the responsible local Ethics Committee in Hamburg and will be conducted according to the principles of the Declaration of Helsinki (2013 version).

### Study population and recruitment

#### Patients

The recruitment of the patients in the IG and CG is carried out by the participating GPs and comprises three guideline-recommended steps of screening and assessment as displayed in Figure 1: First, by applying a 2-item-checklist (*risk-checklist*) the GP systematically identifies those patients with diffuse somatic symptoms and/or with chronic somatic conditions [16,25], i.e. patients at high risk for depression. For this group of patients, the GP continues the screening procedure by using a further guideline-based 2-item-checklist (*main-symptom-checklist*) assessing the main symptoms of depression. A positive answer in at least one of these questions leads to the third screening step, an assessment with the depression module of the Patient Health Questionnaire (PHQ-9): Patients with a score of five or more points meet the study’s basic inclusion criterion and are informed about the study. After giving informed consent, patients receive their baseline questionnaire.

**Figure 1 Fig1:**
[figure not shown]
**Design of the study comparing a stepped care model (SCM) to treatment as usual (TAU) for patients with depression.**

### Inclusion and exclusion criteria

Inclusion criteria are a minimum age of 18, five or more points on PHQ-9 and informed consent. Patients with insufficient knowledge of the German language or a health situation that does not allow questionnaire completion are excluded. Neither somatic nor mental comorbidities are exclusion criteria. However, if a mental disorder other than depression is the main treatment focus patients are also excluded from the study.

### Sample size and power calculation

We aim to gain a sample size that permits a small to moderate effect size between SCM and TAU to be detected with a statistical power of 80%. A small to moderate effect size is defined as eta^2^ = 0.0344 (or f = 0.175 according to Cohen [26]). We expect a reduction of the error variance of approximately 20% by including initial symptom severity (PHQ-9 at t0) as a covariate (which can be expected to be uncorrelated to the study conditions due to randomization). This leads to an adjusted effect size of eta^2^ = 0.042 (f = 0.209). In this respect and based on α = 0.05 a sample of n = 92 patients in each study condition is required for our main analysis. As we presume a drop-out rate of 20% in the IG an initial sample of n = 110 patients is needed in this group to answer the main research question. In order to run further separate analyses for each of the six treatment options within the SCM (and assuming an equal distribution of patients onto each option) we include 6*110 patients in the intervention group. As for the control group, a larger rate of drop-out has to be expected (approximately 50%, due to less personal involvement), a total of N = 200 patients is to be recruited in this study condition. Therefore, a total of N = 860 depressive patients are to be included in the study.

For the primary endpoint changes in PHQ-9 to baseline after 12 months we assume a small to moderate effect size defined as Cohen's d = 0.4 and set the significance level to 0.05 (two-sided). With these settings a sample size of 100 patients in each group is required to achieve a power of 80%. 2 × 100 patients need to be included if the randomization occurs at the patient level. With an assumed intra-cluster correlation (ICC) of 0.05 and 20 included patients per cluster on average a design effect of 1.95 is calculated, increasing the sample size to 200 patients and 10 practices per group.

We decide to recruit the threefold number of patients in the intervention group because we would like to obtain detailed knowledge about the six treatment options. And so we assume to have a sufficient number of patients in each of the treatment options. This approach results in 860 patients and 40 practices to recruit with a 3:1 allocation to the intervention and the control group, respectively.

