### Training and quality standards

Previous to the implementation of the SCM, participating care providers obtain training regarding the recommendations of the German National Clinical Practice Guideline for unipolar depression [18], the rationale and the treatment concept of the SCM and the specific interventions. Each GP is additionally visited by the study team at least once in his or her practice to review the diagnostic routines in the everyday routine care. The psychotherapist for the telephone-based treatment receives special training and weekly supervision. Within the network, guideline-based quality standards are defined (e.g. type and frequency of monitoring). To ensure that these standards are met and to promote the cooperation and information exchange between the participating care providers, quarter-yearly quality circles take place. For the conception of the initial training and quality circles we could integrate experiences from former projects [32–35].

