### Intervention for the control group

Patients in the control condition receive treatment as usual by their GP and within the regular German health care system. However, systematic screening with the risk-checklist, main-symptom-checklist and PHQ-9 are carried out in both intervention and control group to ensure a comparable recruitment and inclusion process.

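### Baseline PHQ-9 being uncorrelated with arm is not assured when allocated, unmasked GPs recruit the patients, and the confirmatory model adjusts for no other patient-level prognostic factor

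*Protocol article*

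**What the plan says.** All references are to the protocol article.

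- **Randomization.** Practices, not patients, are allocated 3:1 by minimisation on practice size, location and district income, giving 36 intervention and 13 control practices. The section presents this as balancing confounders and securing internal validity.
- **Study design.** A patient's arm is that of the recruiting GP. The sample is described as consecutive.
- **Study population and recruitment, Patients.** "The recruitment of the patients in the IG and CG is carried out by the participating GPs". The GP applies two short checklists and the PHQ-9 with a cut-off of 5, informs the patient and, after consent, hands over the baseline questionnaire.
- **Diagnostic process and treatment selection; Training and quality standards.** Intervention GPs carry out arm-specific diagnostics. "Previous to the implementation of the SCM, participating care providers obtain training".
- **Intervention for the control group.** The same screening is used in both arms "to ensure a comparable recruitment and inclusion process".
- **Sample size and power calculation.** "We expect a reduction of the error variance of approximately 20% by including initial symptom severity (PHQ-9 at t0) as a covariate", and this covariate is one "which can be expected to be uncorrelated to the study conditions due to randomization".
- **Statistical analyses.** The only confirmatory analysis is a linear mixed model with group, a random practice effect and baseline PHQ-9. The minimisation factors are examined in addition, outside that model.

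**The concern.** Randomising practices makes the practices comparable in expectation. It carries over to the patients only if recruitment after allocation works the same way in both arms. Here the recruiter belongs to an arm and, in the intervention arm, must know it. No masking of recruiters and no identification of patients before allocation is described. Intervention GPs can offer faster referral and treatments that routine care lacks, so who is approached and who agrees could differ. The protocol itself expects engagement to depend on arm: it assumes about 50% drop-out in the control group and 20% in the intervention group.

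If recruitment did differ, patients with equal PHQ-9 scores could still differ by arm in chronicity, earlier treatment or social position. Adjustment for PHQ-9 alone would not remove the effect of such differences on the 12-month contrast, and the random practice effect deals with clustering, not with selection.

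**Working it through.** **1. The plan's own figure.** "based on α = 0.05 a sample of n = 92 patients in each study condition is required for our main analysis". The inputs are the stated adjusted f = 0.209, two-sided α = 0.05 and 80% power. For two groups d = 2f = 0.418. The normal approximation n = 2(1.96 + 0.84)²/d² gives 90 per group and the t-test gives 91. Power at 92 is 0.805. The figure reproduces to within 2 patients.

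**2. What if baseline PHQ-9 does correlate with arm?** With correlation ρ, the variance of the adjusted group effect grows by 1/(1 − ρ²). For two equal groups, ρ corresponds to a baseline difference of 2ρ/√(1 − ρ²) within-group SDs.

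| ρ | Baseline difference (SD) | 1/(1 − ρ²) | n per condition, from 92 |
|---|---|---|---|
| 0.1 | 0.20 | 1.010 | 93 |
| 0.2 | 0.41 | 1.042 | 96 |
| 0.3 | 0.63 | 1.099 | 102 |

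Even a large baseline difference costs about 10 patients per condition. The second calculation (d = 0.4, 100 per group, design effect 1 + 19 × 0.05 = 1.95) does not use the assumption at all. The planned 660 and 200 are far above these numbers. The sample size is not where the problem lies.

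**3. What the model covers.** Baseline PHQ-9 is a covariate, so a difference in measured PHQ-9 is adjusted for. Other prognostic factors are not. Table 2 shows that sociodemographics, former depression-specific treatments and symptom course are collected at t0, but none of them enters the confirmatory model.

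**4. Illustration of size (assumed inputs; none is in the document).** Suppose a factor worsens 12-month PHQ-9 by 2 points at equal baseline, and its prevalence differs between arms by 10 to 25 percentage points. Shift = imbalance × effect:

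- 0.10 × 2 = 0.2 points
- 0.25 × 2 = 0.5 points

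With an assumed SD of 5, the target d = 0.4 is 0.4 × 5 = 2.0 points. The shift is then 10% to 25% of the target, or 0.04 to 0.10 SD.

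**5. What such a shift would do to the test.** With all 660 and 200 patients analysed and a design effect of 1.95, SE = √[1.95 × (1/660 + 1/200)] = 0.113 SD. With the expected 20% variance reduction it is 0.113 × √0.8 = 0.101 SD. If there were no true effect, the two-sided rejection rate would be:

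| Shift (SD) | Rejection rate |
|---|---|
| 0 | 5% |
| 0.04 | about 6.5 to 7% |
| 0.10 | about 14 to 17% |

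More patients would not reduce such a shift.

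**The case against.** The strongest case against has five parts.

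- **The statement is narrow.** It concerns one variable, in one of two power calculations, and that variable is in the model. This stands: deleting or rewording the statement would by itself change neither the sample size nor any bias.
- **There are safeguards.** A consecutive sample, fixed checklists and a fixed PHQ-9 cut-off limit the GP's discretion. They do so if followed. What remains is the GP's judgement on who is at risk and on whether another mental disorder is the main treatment focus, and the patient's decision to consent.
- **The plan knows the other variables.** Table 2 lists them among its controlling variables, and exploratory subgroup analyses by sex, socio-economic status and severity are planned. Adjusted sensitivity analyses and recruitment flow may also stand in a full protocol or analysis plan that is not shown, so their absence is not criticised here. The published confirmatory model is nevertheless specified with PHQ-9 as its sole patient covariate.
- **A single-covariate model is legitimate.** It is. The case for more covariates is that they are already collected and cost little.
- **Covariates cannot cure selection.** They remove bias only from what they measure. Selection on willingness or motivation would remain.

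A reader might go further and infer that the primary estimate is biased. The document does not show this: differential recruitment is possible, but its existence, direction and size are unknown. A reader might also take 13 against 36 practices as the source of bias. Few clusters raise the risk of chance imbalance, which is not bias. Nor is the sample size wrong on this account.

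**Conclusion.** The point holds in a limited form. That baseline PHQ-9 is uncorrelated with arm is not assured by randomising practices; it needs recruitment that does not differ by arm. The effect on sample size is small (92 becomes at most 102 for ρ up to 0.3). What is left open is imbalance in prognostic factors other than PHQ-9, which the confirmatory model does not address.

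This rests on reading the sections together: that allocation precedes recruitment and that intervention GPs know their arm is clearly implied, but not said in one sentence. The size of any bias cannot be estimated from the document. The range of 0.2 to 0.5 PHQ-9 points follows from assumed inputs and shows only that a moderate imbalance would not be negligible against a target of about 2 points at SD 5. The point warrants an inexpensive improvement to the model, not a finding that the trial's result would be invalid.

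**What to change.** 1. **Primary model.** Pre-specify a small set of t0 covariates as fixed effects beside group and baseline PHQ-9: age, sex, education, former depression-specific treatments and symptom course. All are collected already and are unlikely to be shifted by knowledge of the arm. Leave out t0 items that could be, such as shared decision-making and treatment expectations. The treatment-history and symptom-course items are self-developed and the article gives no scoring, so fix their coding in advance. Use simple imputation for missing covariate values.
2. **Sensitivity analysis.** Keep the model with PHQ-9 as the only patient covariate.
3. **Wording.** In the sample-size section, say that zero correlation between baseline PHQ-9 and arm is an assumption that holds only if recruitment does not differ by arm.
4. **Recruitment by arm.** Compare screening and inclusion between arms as far as the existing screening forms allow. The article does not say that they record eligible patients who decline, so a comparison of consent may not be possible.

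Cost: slightly more analysis work and a few degrees of freedom. Items 1 to 3 need no new data. There is still no protection against selection on unmeasured factors such as motivation.

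### The 860 patients in 40 practices join two separate calculations: the clustered one gives 800, and the printed power refers to 10 + 10 practices, not the 36 + 13 randomised

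*Protocol article*

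**What the plan says.** The section Sample size and power calculation of the protocol article holds two calculations, one after the other.

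The first makes no allowance for clustering. It needs 92 patients per condition, raises this to 110 for 20% drop-out, and multiplies by the number of treatment options: "we include 6*110 patients in the intervention group". The control group is put at 200 because about 50% drop-out is expected there. The total is 860.

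The second uses Cohen's d of 0.4 at a two-sided 5% level, with 100 patients per group for 80% power. It then takes account of clustering: "intra-cluster correlation (ICC) of 0.05 and 20 included patients per cluster on average a design effect of 1.95 is calculated". The consequence for the size of each arm is given as "increasing the sample size to 200 patients and 10 practices per group". The next paragraph states: "We decide to recruit the threefold number of patients in the intervention group". It concludes: "This approach results in 860 patients and 40 practices to recruit with a 3:1 allocation to the intervention and the control group, respectively".

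The Randomization section refers to 49 participating practices, assumes that each GP can recruit 15 to 25 patients, gives a 3:1 ratio for allocating practices, and reports: "A total of 36 practices is randomized into the IG and 13 practices into the CG". The abstract repeats 660 and 200 patients.

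**The concern.** The concluding sentence credits both numbers, 860 and 40, to the cluster calculation followed by tripling. Only the 40 can be obtained that way; the 860 belongs to the unclustered calculation. The splice is easy to miss because the control arm is 200 in both. In the first calculation, though, that 200 allows for about 50% drop-out, and in the second it is the cluster-adjusted requirement with no drop-out allowance stated.

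In a cluster-randomised trial the number of practices and the number of patients per practice determine the design effect, and so the power. The printed design effect and power rest on 20 patients per practice and 10 practices in each arm. The trial described elsewhere in the same article has unequal arms, 36 and 13 practices, and on the stated patient totals fewer than 20 patients per practice in both arms. A reader who wants the power of the described design cannot take it from the printed figures.

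**Working it through.** **Inputs.** From Sample size and power calculation: d = 0.4; two-sided α = 0.05; power 80%; 100 per group; ICC 0.05; 20 patients per practice; 660 and 200 patients; losses of 20% and about 50%. From Randomization: 36 and 13 practices.

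**Step 1: reproduce the plan's cluster calculation.**
- Individually randomised size: n = 2(1.96 + 0.842)²/0.4² = 98.1, so 99 per group (99.1 with the t distribution). The plan's 100 is a fair rounding.
- Design effect: 1 + (20 − 1) × 0.05 = 1.95, exact.
- 100 × 1.95 = 195, rounded up in the plan to 200; 195/20 = 9.75, so 10 practices per group.

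All of this reproduces.

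**Step 2: apply the threefold rule.**
- Intervention: 3 × 200 = 600 patients, 600/20 = 30 practices.
- Control: 200 patients, 10 practices.
- Total: 800 patients in 40 practices.

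The 40 reproduces and the 860 does not. The difference is 60 patients, or 60/860 = 7%.

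**Step 3: find the source of 860.**
- 6 × 110 = 660, and 660 + 200 = 860: the first, unclustered calculation.
- Patient ratio: 660/200 = 3.3.
- Practices needed at 20 each: 860/20 = 43 (33 + 10).
- Keeping both 860 and 40 implies 860/40 = 21.5 per practice (660/30 = 22 and 200/10 = 20).

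**Step 4: design effect and power for each design.** In each arm m = n/k, where k is the number of practices, and DE = 1 + (m − 1) × ICC. Then SE = √(DE₁/n₁ + DE₂/n₂) in standard deviation units, and power = Φ(0.4/SE − 1.96). After loss, 660 × 0.8 = 528 and 200 × 0.5 = 100.

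| Design (patients/practices) | Mean per practice | DE | Power |
|---|---|---|---|
| 200/10 v 200/10 | 20; 20 | 1.95; 1.95 | 81.7% |
| 600/30 v 200/10 | 20; 20 | 1.95; 1.95 | 93.9% |
| 660/30 v 200/10 | 22; 20 | 2.05; 1.95 | 94.2% |
| 660/36 v 200/13 | 18.3; 15.4 | 1.87; 1.72 | 96.3% |
| 528/30 v 100/10 (after loss) | 17.6; 10.0 | 1.83; 1.45 | 84.7% |
| 528/36 v 100/13 (after loss) | 14.7; 7.7 | 1.68; 1.33 | 87.5% |

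Worked line for 660/36 v 200/13: DE₁ = 1 + 17.33 × 0.05 = 1.867 and DE₂ = 1 + 14.38 × 0.05 = 1.719. The effective sizes are 660/1.867 = 353.6 and 200/1.719 = 116.3. SE = √(1/353.6 + 1/116.3) = 0.107, so 0.4/0.107 − 1.96 ≈ 1.78 and Φ(1.78) ≈ 0.963.

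**Step 5: sensitivity.** A t reference on the number of practices minus 2 lowers the 36 + 13 figures to 95.6% at full recruitment and 86.1% after loss. Over an assumed ICC range of 0.02 to 0.10 (the article gives only 0.05), power with 36 + 13 practices runs from 99.1% to 87.9% at full recruitment and from 92.7% to 78.5% after loss.

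**The case against.** Much can be said for the plan.

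- A reader might infer that 40 and 49 practices contradict each other. The documents do not support that: 40 is a number to recruit and 49 the number participating, so a target may simply have been exceeded. The article does not say so, but nothing rules it out.
- A reader might infer that 36:13 breaks the 3:1 ratio. An exact 3:1 split of 49 is 36.75:12.25, so 36:13 is within one practice of it, and minimisation on three factors need not hit the ratio exactly.
- The 3:1 ratio is stated for practices, and 30:10 meets it exactly. The 660 is derived openly as 6 × 110, and threefold may be loose wording for 3.3.
- Recruitment per practice is not left open: the Randomization section assumes 15 to 25 patients per GP, and the means before loss (22, 20, 18.3, 15.4) all lie in that range.
- With 21.5 patients per practice the design effect would be 1 + 20.5 × 0.05 = 2.025 against 1.95, a difference of about 4% on a figure that already rests on an assumed ICC.

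All of this stands, and it narrows the point. It does not rescue the concluding sentence, which assigns 860 to a calculation that yields 800. Nor does it make the printed design effect and power describe the 36 + 13 design.

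**Conclusion.** The sample-size conclusion is wrong as written. The clustered calculation with a threefold intervention arm gives 800 patients in 40 practices; 860 is carried over from the unclustered one. The printed 80% power and design effect of 1.95 apply to 10 + 10 practices at 1:1. They are not figures for 660 patients in 36 practices against 200 in 13.

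This is a minor reporting error. A reader might infer that the trial is underpowered, but the figures do not support that. The randomised design has more practices in both arms and smaller clusters, so the correction is favourable: about 96% power at full recruitment and about 87.5% after the stated losses. Randomisation and the primary analysis are untouched.

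These power figures rest on d = 0.4, an ICC of 0.05, equal practice sizes within each arm and the normal approximation. At an assumed ICC of 0.10, power after loss falls just under 80% (78.5%). They treat lost patients as absent and do not model the planned carrying forward of baseline values, nor any gain from adjusting for baseline PHQ-9.

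**What to change.** In Sample size and power calculation:

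1. Replace the threefold statement by saying that the intervention arm is set at 660 patients (6 × 110, about 3.3 times the control arm), and stop attributing 860 to the cluster calculation.
2. Keep 40 practices, labelled as the planning target, and give 49 (36 + 13) as the number randomised. The target is part of the planning record and should not be deleted.
3. Restate design effect and power for 660/36 against 200/13: means of 18.3 and 15.4 patients per practice, design effects of about 1.87 and 1.72, and power of about 96% at full recruitment and 87.5% after 20% and 50% loss, with the ICC and effect size named.
4. Say whether the 200 control patients are meant as the cluster-adjusted requirement or as the number that allows for drop-out.

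The cost is a few corrected sentences and figures. Recruitment, allocation and analysis do not change.
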